## Abstract

Dietary quality and sustainability are central matters to the international community, emphasised by the burden of the COVID-19 pandemic. To promote healthier and more sustainable food-related practices, the protocol of a web-based intervention to enhance adults’ food literacy is presented. The FOODLIT-Trial is a two-arm, parallel, experimental, and single-blinded randomised controlled trial delivered over 11 weeks. Based on the Food Literacy Wheel framework and supported by the Health Action Process Approach (HAPA) and the Behaviour Change Techniques Taxonomy, weekly content with customised behaviour change techniques (experimental group) is hypothesised to be more effective to promote food behaviour change when compared to a single-time and non-customised delivery of food-related international guidelines, with no theoretically informed approaches (comparison group). Primary outcome is food literacy, including food-related knowledge, skills, and behaviours, assessed with the FOODLIT-Tool; a secondary outcome includes psychological mechanisms that efficaciously predict change in participants’ food literacy, measured with HAPA-driven items. Enlisted through online sources, participants will be assessed across five time points (baseline, post-intervention, and 3-, 6-, and 9-month follow-ups, i.e., T0–T4). A randomisation check will be conducted, analyses will follow an intention-to-treat approach, and linear two-level models within- (T0–T4) and between-level (nested in participants) will be computed, together with a longitudinal mediation analysis. If effective, the FOODLIT-Trial will provide for a multidimensional and cost-effective intervention to enable healthier and more sustainable food practices over the long term.

## 1. Introduction

Both adequate nutrition and worldwide environmental sustainability are strongly sustained by global food systems. In the last decades, imposed by diverse anthropogenic sources, such as growing population and uncertainty of global economy, food systems have been facing major alterations that have deeply impacted food consumption behaviours [1,2,3]. Intricately linking human health and sustainability, food consumption patterns represent one of the greatest challenges of this century. Trending unhealthy meal patterns, often driven by needs of convenience and inadequate accessibility to nutritious foods, are characterised as high in caloric value, excessively processed, and rich in animal source foods [3,4]. Leading to over 2 billion adults with overweight or obesity and a global prevalence of non-communicable diseases such as diabetes, unhealthy diets pose a greater risk to morbidity and mortality than those of unprotected sex, alcohol, tobacco, and drug use combined [3,5]. Moreover, with the global public health pandemic of COVID-19, food consumption behaviours are demonstrating an increased pattern of unhealthier diets during home confinements and other related restrictions across diverse countries [6].

Additional to increasing the burden of food-related diseases, these unhealthy dietary trends also play a crucial role in environmental degradation [7,8]. Food regimes identified as lose–lose diets—characterised by being both unhealthy and environmentally unsustainable—are not only described as high in saturated fats, added sugars, and red meats, but also represent a higher environmental burden, being associated with the transformation of natural ecosystems into croplands and threatening biodiversity with species’ extinction [9]. With 40% of global land occupied by agriculture, and food production being accountable for up to 70% of freshwater use and 30% of worldwide greenhouse-gas emissions, a change in the global food system is needed to minimise its impact on both human health and environmental sustainability [3,10,11,12].

A shift towards improved nutrition and more sustainable food systems has been a concern to the international community, represented by global agendas such as the Sustainable Development Goals integrated within the 2030 Agenda [13], its Food Systems Summit [14], and the Decade of Action on Nutrition [15]. However, this shift will not thrive without a simultaneous bottom-up transformation; it is crucial that people change how they view, understand, and engage with food systems, ultimately changing their food-related knowledge, competencies, and behaviours—that is, their food literacy [3,4,16,17].

### 1.1. Food Literacy

Designated as crucial to protect the quality of diets across the lifespan, food literacy has been gaining prominence across research, practice, and policy during the last decade [18,19,20,21,22,23]. Generally seeking to improve nutrition knowledge and food-related skills, most programmes and interventions developed within the scope of food literacy either (i) exclusively feature nutrition information [24,25,26], (ii) are targeted towards younger populations and often developed in an educational context [27,28,29,30,31], and/or (iii) narrowly focus on preparation or cooking skills, not emphasising other food-related competencies (e.g., planning, acquisition) [21,25,28,32]. More importantly, current interventions do not provide for knowledge to face the complexity of today’s food environment, nor the competencies to deal with it and navigate within aiming for healthier food patterns; consequently, food-related behaviour change is limited [32].

Acknowledging the intertwined relation among food system stakeholders and individuals’ food literacy, and its relevance in order to tackle major challenges concerning global sustainability, this team developed the Food Literacy Wheel (FLW) [16] and the FOODLIT-Tool [17]. The first is a conceptual and empirical framework of food literacy, comprehending not only the set of food-related knowledge, competencies, and behaviours but also its determinants (such as convenience and practicality, time and financial management, access to food information, and professionals’ unpreparedness on food-related expertise) and influential factors (psychological and learning surroundings, policy and industry settings, sustainability and social contexts, among others). The second concerns a validated and reliable instrument to assess the food literacy of adults based on the FLW; this quantitative measure allows for its own tailoring to diverse contexts and intends to evaluate one’s food literacy, its determinants, and influential factors, as a resource to promote behaviour change towards more healthier and sustainable food habits.

Aiming to make a contribution for the development of food-related competencies, attainment of healthier eating habits and achievement of more sustainable practices within one’s diet, the FOODLIT-Trial will integrate both the FLW and the FOODLIT-Tool on a digital intervention to promote food literacy and sustainability behaviours in adults.

### 1.2. Digital Interventions to Promote Behaviour Change

The use of technology within the daily life of developed countries’ population has gained particular relevance in recent years, being even more emphasised by the current COVID-19 global pandemic. With almost 90% of European households having online access and more than 70% adults affirming the use of online resources on an everyday basis, studies conducting digital interventions aiming for behaviour change have become widespread [33,34,35]. Particularly in the scope of health promotion, food consumption has been one of the most mainstream topics for the use of digital technologies; accounting for daily activities, the potential for food-related behaviours (such as purchasing, cooking, or eating) to be changed through digital solutions, such as web-based self-guided programmes and smartphone applications, is significantly appealing [35,36]. However, with the increase in digital interventions for the promotion of food-related healthier and sustainable behaviours, various trends have emerged. Within the theme of food sustainability, targeted behaviours have mainly focused on the reduction of food waste [37,38,39,40]; food-related competencies, purchasing, and cooking have been the most recurrent aimed behaviours [41,42,43]. The predominance of programmes targeted at younger populations [44,45] or specific to clinical conditions [46,47] is also notorious. Particularly concerning food literacy, the use of digital tools to promote food-related knowledge, competencies, and behaviours is still taking its first steps; either featuring technology or not, the prevalence of a younger target across food literacy interventions and programmes is evident [22,31,32,48]. More recently, however, the adult population has been targeted in research-based interventions [49,50,51,52], and digital resources remain scarce in the field.

Another noticeable characteristic of digital interventions to promote for healthy, sustainable, and knowledgeable food-related behaviours is the lack of clear theoretical backdrop to sustain behavioural change. The majority of these studies are scarcely grounded on a behavioural change theory [37,38]; most report an increase in participants’ awareness but do not explore longitudinal and evidence-based behaviour change [35]. Limitations of previous studies include lack of baseline data, lack of control or comparisons group, and lack of longitudinal follow-up data [35,43,49].

Addressing the promotion of healthier and more sustainable food-related knowledge, competencies, and behaviours through a digital and online intervention, the FOODLIT-Trial is grounded in the Health Action Process Approach (HAPA) [53,54] and applies behaviour change techniques from a consensual taxonomy (Behaviour Change Techniques Taxonomy (BCTT)) [55], aiming to lead to effective and sustained food behaviour change.

### 1.3. Study Objectives and Hypothesis

This study presents the detailed research protocol of a randomised controlled trial (RCT) to assess the efficacy of a web-based intervention in enhancing adults’ food literacy, using (i) digital evidence-based resources, (ii) behavioural change techniques from the BCTT [55], and (iii) the HAPA framework [53,54] as a theoretical backdrop.

The study’s primary objective is to evaluate whether the developed digital intervention is effective in improving food-related knowledge, competencies, and behaviours, based on the FLW [16] and evaluated with the FOODLIT-Tool [17]. Potential differences in participant’s food literacy over time will also be assessed with a longitudinal design. We hypothesise that the use of a web-based intervention combined with behavioural change strategies (customised to each food-related skill) will be more effective to enhance food literacy than the approach used with the comparison group (single-time delivery of non-customised food-related national and international guidelines, without any additional theoretically informed, evidence-based behaviour change approaches). The second objective is to understand the intervention performance, by evaluating which psychological mechanisms, such as self-efficacy, planning, and action control [53,54], efficaciously determine change in participants’ food literacy. It is hypothesised that HAPA-derived mechanisms will significantly mediate the participants’ outcomes concerning food literacy.

## 2. Methods and Analysis

### 2.1. Trial Design

The FOODLIT-Trial is a two-arm (allocation ratio 1:1), parallel, experimental, and single-blinded randomised controlled trial for Portuguese adults (Figure 1). The web-based intervention is delivered over 11 weeks, where each week is themed with content either according to the FLW framework or to the HAPA model.

In conformity to the week’s thematic, each ability, skill, and behaviour is matched with a behavioural change strategy to facilitate its implementation [55]. All measures will be assessed at five time points: baseline (T0), to measure baseline characteristics, pre-intervention, before randomised allocation, and prior to the trial’s first week; post-intervention (T1); one week after the 11-week intervention delivery; and at follow-up times 3, 6, and 9 months after the intervention (T2, T3, and T4, respectively).

This protocol adheres to the Consolidated Standards of Reporting Trials [56] guidelines for randomised controlled trials.

### 2.2. Ethical Approval

As part of a major project titled FOODLIT-PRO: Food Literacy Project, this study was approved by the Ethics Committee of Ispa—Instituto Universitário (ref. D/002/03/2018). The FOODLIT-Trial was developed according to the Declaration of Helsinki, followed the deontological norms and ethical principles of the Order of Portuguese Psychologists [57], and adhered to General Data Protection Regulation [58]. This protocol was approved and registered by ClinicalTrials.gov (NCT04806074).

### 2.3. Participants and Recruitment

Considering its web-based format, FOODLIT-Trial’s potential participants will represent a sample of convenience and snowballing, and will be reached and enlisted through online sources. Online reach out will be made by using both advertisements in social media websites according to the researcher’s network (Instagram and Facebook, Meta Platforms: Cambridge, MA, USA) and a developed website for participants’ enrolment. During the recruitment stage, potential participants will be informed that trial participation will entail compensation in order to acknowledge their time and effort dedicated to the study.

An a priori power analysis was conducted with G*Power (v. 3.1), and a minimum sample size of 28 was necessary in order to detect a medium effect size (Cohen’s d = 0.50) at the 5% level of significance with 95% power, with the assumption of the non-violation of sphericity (non-sphericity correction ε = 1) considering the trial’s repeated-measures design. Given a potential attrition rate of 50% due to the digital nature of the trial, its duration, and required weekly assessments, a minimum of 56 participants will be recruited.

Participants for the FOODLIT-Trial must (i) be adults aged 18 years or older, (ii) be able to understand and read Portuguese, (iii) have availability to engage in the 11-week trial, and have internet access that allows for their engagement, (iv) be responsible for, at least, one out of four tasks in their food routine (encompassing choice and decision, selection and acquisition, preparation, and cooking, according to [18]). Potentially eligible participants will be invited to the trial through an online information sheet, and will be provided with the consent form; if eligible, the baseline questionnaire (T0) will be made available and delivered online. Additionally, all participants will be asked to complete a sociodemographic questionnaire aiming to collect self-reported data concerning sociodemographic and health-related characteristics (e.g., sex, age, educational level, diagnosed diseases, height, weight).

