### 3.2. Hypotheses Tests for Intervention Effects

Linear two-level models with five time points (T0, T1, T2, T3, T4; within-level) nested in participants (between-level) will be computed. For each outcome measure, time (linear day trend, centred at 0) x experimental condition (0 = comparison condition; 1 = intervention condition) interactions will be estimated. Moreover, grand-mean centred covariates (e.g., sex, age) will be added as between-level predictors. The linear time trend and the linear time trend x experimental condition interaction will be modelled as fixed effects.

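### The stated 95% power for d = 0.50 with 28 participants does not hold for the two-arm comparison that the trial tests; the planned time-by-condition test has roughly 21–47% power at 28

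*Protocol article*

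**What the plan says.** Section 2.3 reports an a priori G*Power calculation: "a minimum sample size of 28 was necessary in order to detect a medium effect size", given as Cohen's d = 0.50, "at the 5% level of significance with 95% power". It was done "with the assumption of the non-violation of sphericity" ("non-sphericity correction ε = 1"), "considering the trial’s repeated-measures design". Allowing for 50% attrition, at least 56 are to be recruited. The paragraph does not name the test or the correlation between repeated measures, and it does not say which contrast d = 0.50 describes.

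Section 2.1 sets two arms at 1:1 and five assessments (T0 to T4), so 28 completers are 14 per arm. Section 1.3 hypothesises that the web-based intervention improves food literacy more than the comparison condition does. Section 3.2 gives the test: "Linear two-level models with five time points (T0, T1, T2, T3, T4; within-level) nested in participants (between-level) will be computed", with the linear time trend and its interaction with condition as fixed effects. Section 3.1 specifies intention to treat, with full information maximum likelihood for missing values.

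**The concern.** The only hypothesis for the primary outcome is a between-arm one, so a reader will take d = 0.50 as a difference of half a standard deviation between arms. Fourteen per arm is far too few to detect that with 95% power by any usual between-arm analysis. A repeated-measures calculation can return a number as small as 28, but only because its effect-size parameter f measures how the visit-by-arm profile varies. In that setting f = 0.25 is not the same as a between-arm d of 0.50, although the two are paired in the familiar one-way conversion f = d/2.

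What is at stake is how the result is read. With a stated 95% power, a non-significant interaction could be taken as good evidence against a medium effect. The actual risk of missing such an effect is much greater than 5%.

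**Working it through.** **Inputs from the protocol article.** Two arms at 1:1; five visits; α = 5% (taken as two-sided); target power 95%; d = 0.50; ε = 1; N = 28 completers (14 per arm), 56 recruited (28 per arm). **Assumed, because not stated:** an equal correlation ρ between visits, range 0.5–0.7, with unit SD at each visit.

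**1. The plan's own figure.** For a repeated-measures ANOVA interaction with two groups and m = 5, λ = f²·N·m·ε/(1−ρ), with df (m−1) = 4 and (N−2)(m−1) = 104. With f = d/2 = 0.25 and N = 28, λ = 0.0625 × 28 × 5/(1−ρ) = 8.75/(1−ρ).
- ρ = 0.50: λ = 17.5, power 92.5%.
- ρ = 0.55: λ = 19.4, power 95.0%.
- ρ = 0.58: λ = 20.8, power 96.3%.

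So 28 is the minimum for five visits when ρ is about 0.55–0.58. The attrition step is right: 28/(1−0.5) = 56.

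**2. What f = 0.25 means as a between-arm difference.** Write the arm differences over T0–T4 as (0, d, d, d, d). Their mean is 0.8d and their variance is (0.64 + 4 × 0.04)d²/5 = 0.16d². For an interaction in two equal arms, f = √(variance/4) = 0.2d. Hence f = 0.25 corresponds to d = 0.25/0.2 = 1.25 SD at every visit from T1 to T4. A sustained d = 0.50 is f = 0.2 × 0.50 = 0.10. At f = 0.10 and N = 28 this F test has 22% power (ρ = 0.5) to 36% (ρ = 0.7). The translation from f to d does not involve ρ.

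**3. The planned linear time × condition test.** Visits fall at about weeks 0, 12, 24, 37 and 50 (T1 one week after the 11 weeks; follow-ups 13, 26 and 39 weeks after the intervention). The mean is 24.6 and Sxx = Σ(t − 24.6)² = 1563.2. With n per arm, the SE of the slope difference is √[2(1−ρ)/(n·Sxx)]. The test is a t test on 8n − 2 df.
- Sustained 0.50 SD from T1: fitted slope difference = 0.5 × 24.6/1563.2 = 0.00787 SD per week.
- Linear divergence to 0.50 SD at T4: slope difference = 0.5/50 = 0.0100 SD per week.

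For n = 14 and ρ = 0.5, SE = √[1/(14 × 1563.2)] = 0.00676, so the noncentrality is 1.16 (sustained) or 1.48 (linear).

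| True pattern | N = 28, ρ = 0.5 | N = 28, ρ = 0.7 | N = 56, ρ = 0.5 | N = 56, ρ = 0.7 |
|---|---|---|---|---|
| Sustained 0.50 SD from T1 | 21% | 32% | 37% | 56% |
| Linear to 0.50 SD at T4 | 31% | 47% | 55% | 77% |

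**4. Other between-arm analyses at d = 0.50, as a bracket.**
- Two-sample t test at one visit: noncentrality 0.5 × √(n/2) = 1.32 (n = 14) or 1.87 (n = 28), power 25% or 45%. Power of 95% needs 105 per arm.
- Baseline-adjusted mean of T1–T4, the most favourable analysis tried: residual variance (1 + 3ρ)/4 − ρ² = 0.375, 0.285 and 0.21 for ρ = 0.5, 0.7 and 0.8. At 28 completers this gives 55%, 66% and 79%.

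**5. Difference detectable with 95% power.** For the one-visit t test with 14 per arm, solving for d gives about 1.4 SD.

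**The case against.** Four points can fairly be made for the plan.

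**The 28 can be reproduced.** A reader might infer that it is an arithmetic slip: that it fails for five visits, that six measurements were entered, or that the count should be 32 (64 recruited). The document does not support this. At G*Power's default correlation of 0.5, five visits need 32, and 28 matches six measurements. But no correlation is stated, and at about 0.55–0.58 the answer for five visits is 28. Even at 0.5 the gap is only 92.5% against 95%. Moving to 32 would also leave the effect-size problem untouched.

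**Sphericity is a declared assumption.** A reader might want a smaller ε, such as 0.6. Nothing in the document supplies such a value, and ε does not enter the planned linear-slope test.

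**Section 2.3 never calls d = 0.50 a between-arm difference.** That is correct; the reading comes from the hypothesis in section 1.3 and the test in section 3.2. If d meant something else, the paragraph would give no power for the trial's own hypothesis.

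**Counting only 28 completers is pessimistic.** This stands. Full information maximum likelihood uses the visits that drop-outs did complete, so the effective sample lies between 28 and 56. With all 56 retained, the planned test reaches 77% at best for correlations of 0.5–0.7, so it cannot be said that a medium effect would be missed most of the time in every scenario. The baseline-adjusted mean of T1–T4 would do better still with 56: 85%, 93% and 98% at correlations of 0.5, 0.7 and 0.8. That is not the planned test, however, and the article attaches its 95% to 28, not to 56.

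**Conclusion.** The point holds as a mismatch of effect size. The statement that 28 participants give 95% power for d = 0.50 is wrong for the two-arm hypothesis under the planned test. At 28 completers, power for a true 0.50 SD difference is about 21–47%, depending on whether the effect is sustained or grows linearly; with all 56 retained it is about 37–77%. No between-arm analysis tried reached 95% at 28 for correlations up to 0.8; the best gave 79%.

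The power figures rest on an assumed correlation of 0.5–0.7, equal across visits, and on the approximate visit weeks; a higher correlation would raise them. The conversion of f = 0.25 to a sustained 1.25 SD does not depend on the correlation. That the 28 came from an F test at f = 0.25 is an inference from its size and the wording about sphericity, not something the article states. The power claim needs correcting; the arithmetic behind the 28 is not shown to be in error.

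**What to change.** Rewrite the sample-size paragraph in section 2.3 for the time × condition test of section 3.2. Define d = 0.50 as a between-arm difference, and say at which visits and in what pattern it is assumed. State the correlation used. Then give either the power at both 28 and 56, or the difference detectable with 95% power. For example: with 28 completers (14 per arm) and an assumed correlation of 0.5–0.7, the planned test has about 21–32% power for a sustained 0.50 SD difference and 31–47% for one that grows linearly to 0.50 SD at T4; with 56 retained, 37–56% and 55–77%; the difference detectable with 95% power at a single visit by t test with 28 is about 1.4 SD.

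Add that the between-arm effect will be reported with its 95% confidence interval, and that a non-significant result will not be read as excluding a medium effect.

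The change is one of wording, with no change to the design or analysis. Its cost is a less favourable stated power.
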